# INTRODUCTION

## Background

Worldwide, 170 million people are infected with Hepatitis C (HCV).[^1^](#_ENREF_1) Persons who inject drugs (PWIDs) have the highest burden of HCV in the US and globally. In the US, an estimated 43% of PWIDs have chronic HCV and National HIV Behavioral Surveillance data suggest that 50-60% of all PWIDs have HCV, notwithstanding high levels of sterile syringe use.[^2^](#_ENREF_2) The Centers for Disease Control and Prevention (CDC) estimates at least 18,000 new HCV infections per year, almost exclusively among PWIDs, with a 44% increase in the number of acute cases from 2010 to 2011 and a 50% increase through 2012. The CDC now considers there to be an emerging epidemic of HCV among young PWIDs, due in part to expansions and retractions in opioid prescribing and related transitions to injection drug use that have occurred in communities across the US.[^3^](#_ENREF_3) In San Francisco, HCV incidence among young adult PWIDs is 26%.[^4^](#_ENREF_4) While the hepatic sequelae of HCV may take decades to develop, ongoing use of injection drugs is the principal source of secondary transmission.

Mathematical models suggest that treating PWIDs for HCV could result in substantial reductions in both prevalence and incidence of HCV. “Treatment as Prevention” (TasP), is an approach to prevention whereby treatment is used to decrease the chance of forward transmission. Treating 8% of PWIDs annually for HCV could reduce HCV prevalence—the major driver for incidence—by 90% over 15 years according to a conservative TasP model that assumed that re-infection rates post-treatment were the same as initial infection rates.[^5^](#_ENREF_5) Cohort studies, however, estimate the re-infection rate at 4-6% per year[^6^](#_ENREF_6)^,^[^7^](#_ENREF_7), about half the rate assumed for initial infection, and a study of PWIDs treated with interferon-based therapy demonstrated a re-infection rate of 2.8%[^8^](#_ENREF_8); thus, the impact of TasP may be greater than predicted. An analysis of the use of novel HCV therapeutics found that treating HCV-infected persons will *fail to impact incidence unless delivered to those with early-stage infection*; this is because very few of those at risk of secondary transmission have advanced liver disease.[^9^](#_ENREF_9) Thus, treating to prevent HCV incidence is distinct from treating to prevent hepatic sequelae.

## Ledipasvir/Sofosbuvir Fixed-Dose Combination

LDV/SOF (also known as SOF/LDV) fixed-dose combination combines two HCV specific direct acting antiviral (DAA) agents into a single tablet for the treatment of chronic HCV infection.

## Rationale for the Current Study

Directly observed therapy (DOT) strategies have only recently been evaluated for HCV treatment—to date, data among substance users are promising but involve only interferon-based therapies. A pilot study of pegylated interferon injections administered in a methadone clinic with self-administered twice-daily ribavirin found 100% compliance and high SVR[^10^](#_ENREF_10), as did daily DOT in methadone and buprenorphine treatment programs[^11^](#_ENREF_11). A randomized trial of DOT (for interferon injections only) versus self-administration of all medications among methadone patients found higher SVR rates among those receiving DOT (54% vs 33%). A pilot study of DOT for weekly interferon injections among out-of-treatment PWIDs demonstrated SVR of 58% and no associations between past month drug use and completion of HCV therapy or SVR[^8^](#_ENREF_8). These results suggest that DOT may be beneficial, at least for interferon-based regimens, and that ongoing drug use may not be a significant deterrent to successful HCV treatment. These strategies remain underexplored among actively using PWIDs, the most efficient target group for a TasP initiative, and have not yet been tested for novel HCV therapies.

This study will test the acceptability of a once daily DAA regimen for HCV among actively injecting PWIDs. Active substance users have been excluded from clinical trials of DAAs. Given the high cost of LDV/SOF ($1200/pill) and the limits already placed by insurers (such as 6-12 months of abstinence prior to treatment and advanced fibrosis), access to DAAs for PWIDs is likely to remain extremely limited for the near future. This study will assess the acceptability of HCV therapy with DAAs among PWIDs, necessary data not only for future TasP interventions, but also for efforts to improve HCV clinical care for PWIDs.

## Rationale for Dose Selection of Ledipasvir/Sofosbuvir Fixed Dose Combination

LDV/SOF tablet (90 mg/400 mg) administered with or without RBV has demonstrated favorable safety and efficacy profiles in over 3000 HCV‑infected subjects across different patient populations in Phase 2 and 3 trials. These doses represent the marketed doses of ledipasvir and sofosbuvir.

## Overall Risk/Benefit Assessment

This study aims to provide an effective treatment option to PWIDs with HCV infection who currently lack effective treatment options due to their ongoing injection drug use. The results of this study will be used to develop the optimal route of medication delivery for future interventions aiming to treat HCV among persons actively injecting drugs.

The study will be evaluated on an ongoing basis by the UCLA Addiction Medicine Data Safety Monitoring Board.

## Compliance

This study will be conducted in compliance with this protocol, Good Clinical Practice (GCP), and all applicable regulatory requirements.

# OBJECTIVES

The primary objectives of this study are:

- To assess the feasibility of treating active PWIDs for HCV with LDV/SOF by mDOT versus unobserved dosing, with MI adherence counseling, as measured by recruitment and retention rates, overall and by arm.
- To evaluate the acceptability of mDOT versus unobserved dosing, with MI adherence support, among PWIDs treated with LDV/SOF, as determined by mDOT and MI participation rates, medication adherence rates and the proportion of subjects that complete therapy, by arm.
- To assess through in-depth, semi-structured qualitative interviews, the challenges with time intensity required for mDOT and unobserved dosing interventions, and identify key factors affecting treatment adherence for PWIDs treated with LDV/SOF.

Exploratory objectives of this study are:

- To assess end-of-treatment response and SVR, as determined by the proportion with undetectable HCV RNA at weeks 8 and post-treatment week 12, by arm.
- To potentially assess adherence to treatment by weekly SOF metabolite levels, by arm (depending on SVR results) as applicable.
- To assess drug use behaviors before and after HCV treatment.
- To assess HCV relapse and reinfection at post-treatment week 36 among participants achieving SVR.
- To evaluate demographic, behavioral and HCV strain correlates of adherence and SVR.
- To characterize the social and PWID networks of participants in preparation for a subsequent full TasP trial.

# STUDY DESIGN

## Study Treatment and Duration of Treatment

This is an open-labeled study that will evaluate the feasibility, acceptability, and effectiveness of mDOT versus unobserved dosing of 8 weeks of LDV/SOF in genotype 1 HCV–infected persons who actively inject drugs.

Thirty subjects will be enrolled in one of the following two treatment groups.

**Group 1**: Subjects receiving modified directly observed therapy

- - - LDV/SOF tablet (LDV 90mg/SOF 400mg) once daily for 8 weeks (dosing observed daily Monday-Friday).

**Group 2**: Subjects receiving unobserved weekly dosing

- - - LDV/SOF tablet (LDV 90mg/SOF 400mg) once daily for 8 weeks (tablets dispensed weekly and dosing is unobserved).

## Treatment Discontinuation Criteria

Study drug will be discontinued in the following instances:

- Unacceptable toxicity, as defined in Section 7 of the protocol, or toxicity that, in the judgment of the investigator, compromises the ability to continue study-specific procedures or is considered to not be in the subject’s best interest
- Subject request to discontinue for any reason; it is important to determine whether the withdrawal of consent is primarily due to an AE, lack of efficacy, or other reason
- Discontinuation of the study at the request of Gilead, regulatory agency, or an Institutional Review Board (IRB), with appropriate justification

Study drug *may* be discontinued based on individual case review by both study physicians in the event of pregnancy of a female subject.

If a subject meets discontinuation criteria during treatment, an early termination (ET) visit will be required (Section 6.4). All subjects who meet discontinuation criteria will complete an ET visit, which will include all week 8 procedures, and post-treatment visits at weeks 1, 12 and 36, regardless of the treatment duration.

# SUBJECT POPULATION

## Number of Subjects and Subject Selection

Thirty (30) subjects will be enrolled in this study.

At this time, thirty subjects have been successfully enrolled. There is enough study drug left to enroll one more subject in this study. Since there is enough study drug to treat someone, an extra study subject will be enrolled and will follow the same protocol guidelines as the previous subjects.

## Inclusion Criteria

Subjects must meet *all* of the following inclusion criteria to be eligible for participation in this study.

**(1) ≥**18 years of age;

**(2)** 2 consecutive positive HCV RNA tests at least 6 months apart;

**(3)** HCV genotype 1;

**(4)** HCV RNA <6 million copies by Roche TaqMan® Assay

**(5)** No evidence of hepatic cirrhosis (as determined by two indices: Fib4 <3.25 and fibrosis-cirrhosis index (FCI) <1.25;

**(6)** Drug injection in past 30 days by self-report *and* physical exam evidence of injection drug use (e.g., track marks);

**(7)** Injected with others in past 12 months by self-report;

**(8)** Lab values within acceptable range (platelets >50,000, creatinine clearance by Cockroft-Gault ≥60mL/min, hemoglobin >10g/dL, INR <1.5 x upper limit of normal (ULN) unless stable on anticoagulant regimen or known hemophilia, AST/ALT <10 x ULN);

**(9)** Able to speak English;

**(10)** No plans to leave the San Francisco area for at least 9 months and either lives or works in San Francisco, or travels to San Francisco at least weekly;

**(11)** For women of childbearing age, pregnancy test negative, not actively nursing, and agree to use birth control during treatment (although LDV/SOF has a FDA Pregnancy Category rating of B, consistent with no known evidence of harm, treatment is not urgent for these patients so we will err on the side of caution).

## Exclusion Criteria

Subjects who meet *any* of the following exclusion criteria are not to be enrolled in this study.

**(1)** HIV+;

**(2)** HBV surface antigen +;

**(3)** Non-definitive HCV genotype results;

**(4)** Previously received treatment for HCV (interferon, ribavirin, or DAA);

**(5)** Taking medications that affect pharmacokinetics of LDV/SOF (proton-pump inhibitors, anticonvulsants [phenobarbital, phenytoin, carbamazepine, oxycarbazepine], rifamycins, rosuvastatin, herbs [St. John’s wort, silymarin, echinacea]);

**(6)** History of any of the following:

- 1. Current gastrointestinal disorder or post-operative condition that could interfere with the absorption of the study drug
  2. History of hepatic decompensation (i.e., ascites, encephalopathy or variceal hemorrhage)
  3. History of solid organ or bone marrow transplantation
  4. Current treatment for cancer

**(7)** Chronic liver disease for non‑HCV reason (e.g., Wilson’s disease, alpha‑1 antitrypsin deficiency, cholangitis) except iron overload;

**(8)** Use of any prohibited concomitant medications as described in Section 5.2 within 21 days of the enrollment visit; and

**(9)** Known hypersensitivity to LDV, SOF, the metabolites, or formulation excipients.

**(10)** Any other conditions that preclude study involvement as determined by PI.

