## Prior and Concomitant Medications

Concomitant medications taken within 30 days prior to screening will be recorded in the source documents and case report form(s) (CRFs).

Concomitant use of certain medications or herbal/natural supplements (inhibitors or inducers of drug transporters i.e., P‑gp) with study drug may result in PK interactions increasing or decreasing exposure to study drug.  Examples of representative medications which are prohibited from 21 days prior to enrollment through the end of treatment are listed below. The use of amiodarone is prohibited from **60 days prior to enrollment** through the end of treatment. Participants will be advised to avoid selected medications until 21 days after the end of treatment (e.g. digoxin and rosuvastatin)

Table 5‑1. Concomitant Medications Disallowed or to be used with Caution

| Drug Class | Agents Disallowed | Use with Caution |
| --- | --- | --- |
| Acid Reducing Agents^a^ |  | Proton- Pump Inhibitors, H2‑Receptor Antagonists, Antacids |
| Anticonvulsants^b^ | Phenobarbital, Phenytoin, Carbamazepine, Oxcarbazepine |  |
| Antimycobacterials^b^ | Rifabutin, Rifapentine, Rifampin |  |
| Cardiac Medications | Amiodarone^c^ | Digoxin^d^ |
| Herbal/Natural Supplements^b^ | St. John’s Wort, Echinaccea, Milk thistle (i.e., silymarin), Chinese herb sho-saiko-to (or Xiao-Shai-Hu-Tang) |  |
| HMG-CoA Reductase Inhibitors^e^ | Rosuvastatin |  |

a It is recommended to separate antacid and LDV/SOF administration by 4 hours. H2-receptor antagonists may be administered simultaneously with or staggered from LDV/SOF at a dose that does not exceed doses comparable to famotidine 40 mg twice daily. Proton-pump inhibitor doses comparable to omeprazole 20 mg can be administered simultaneously with LDV/SOF. Proton-pump inhibitors should not be taken before LDV/SOF.

b May result in a decrease in the concentrations of study drug.

c May result in symptomatic bradycardia. Mechanism is not currently known. The use of amiodarone is prohibited from 60 days prior to Baseline/Day 1 through the end of treatment.

d May result in an increase in the concentration of study drug and/or concomitant medications. Co-administration of LDV/SOF with digoxin may increase the concentration of digoxin. Caution is warranted and therapeutic concentration monitoring of digoxin is recommended when co-administered with LDV/SOF.

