### Primary Endpoints

- Screen to eligibility ratio, overall
- Eligibility to enrollment rate, overall
- Retention rates, overall and by arm
- Study completion rates, overall and by arm
- Medication adherence rates and the proportion of subjects that complete therapy, overall and by arm
- Barriers and facilitators to HCV treatment

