## Data Analysis

### Primary Analysis

### Feasibility: Feasibility of treating active PWIDs for HCV with LDV/SOF by mDOT versus unobserved dosing will be measured by recruitment and retention rates overall and by arm. We will calculate the following feasibility measures: 1) proportion of those eligible among those screened; 2) proportion enrolled among those eligible; and 3) study retention and completion rates, overall and by arm. Process measures (e.g., visit length) and reactions to study procedures will also be assessed. Descriptive statistics will be presented with 95% confidence intervals, to help in interpretation. Between-group differences in retention and completion will be assessed using Fisher’s exact and Wilcoxon tests. We will also calculate Kaplan-Meier curves for time to dropout, by group, and test for differences using the log-rank test.

**Acceptability:** The acceptability of mDOT versus unobserved dosing, the percent of treatment medication adherence to LDV/SOF, will be measured by the percent of doses taken overall (observed and unobserved), will be assessed using DOT doses and weekend WisePill data for the mDOT arm, and WisePill data for the unobserved dosing arm. Other outcomes of interest will include completion of therapy, patterns of adherence, and time to stopping medication. Concordance of the various adherence measures will be examined using weighted Kappa and intraclass correlations. Between-arm differences will be assessed using Fisher’s exact and Wilcoxon tests for outcomes measured once, and GEE models for repeated outcomes. We will also use GEE models to compare WisePill openings and pill counts, accounting for between-arm differences in expected frequency.

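### Exclusion (5) bars current proton-pump-inhibitor users, but Section 5.2 lists the class under caution only and allows co-administration; the two need reconciling

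*Protocol*

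**What the plan says.** Section 4.3 opens with the rule that people who meet any of the "exclusion criteria are not to be enrolled in this study". Exclusion (5) then covers anyone "Taking medications that affect pharmacokinetics of LDV/SOF (proton-pump inhibitors, anticonvulsants", followed by rifamycins, rosuvastatin and herbs). It sets no dose limit and no time window. Exclusion (8) separately bars "Use of any prohibited concomitant medications as described in Section 5.2 within 21 days of the enrollment visit".

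Section 5.2 introduces its table as examples of medications "prohibited from 21 days prior to enrollment through the end of treatment are listed below". In Table 5-1 the row for acid-reducing agents has an empty disallowed cell, and "Proton- Pump Inhibitors" appear in the caution column with H2-receptor antagonists and antacids. Footnote a adds that "Proton-pump inhibitor doses comparable to omeprazole 20 mg can be administered simultaneously with LDV/SOF", subject to a condition on the order of dosing.

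The first primary endpoint in Section 9.1.2 is "Screen to eligibility ratio, overall". Section 9.5.1 computes it as the "proportion of those eligible among those screened".

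**The concern.** Exclusion (5) gives its reason: the listed drugs alter exposure to the study drug. Section 5.2 deals with the same interaction and reaches a different position for one class. A screener who checks medications against Table 5-1 would find proton-pump inhibitors usable with caution. A screener who checks the exclusion list would turn the same person away.

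Three things depend on which section is followed: who enters, who takes study drug together with a class that the protocol says affects its pharmacokinetics, and how many people count as eligible. The last is a primary feasibility measure in a pilot whose results are to be used in designing a full-scale trial. Exposure also bears on SVR and on any metabolite testing, although Section 9.5.2 treats both as exploratory.

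**Working it through.** The protocol states no figure on this point, so the main check is a comparison of the text.

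**Step 1. Compare each class in exclusion (5) with Table 5-1.**

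| Class named in exclusion (5) | Column in Table 5-1 | Agree? |
| --- | --- | --- |
| Proton-pump inhibitors | Caution; disallowed cell empty | No |
| Four named anticonvulsants | Disallowed | Yes |
| Rifamycins | Disallowed | Yes |
| Rosuvastatin | Disallowed | Yes |
| St. John's wort, silymarin, echinacea | Disallowed | Yes |

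The other caution-column entries (H2-receptor antagonists, antacids, digoxin) are absent from exclusion (5), which is consistent. Proton-pump inhibitors are the only mismatch.

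**Step 2. Apply the entry rules to a current user.** Exclusion (5) is met. Exclusion (8) is not met, because Table 5-1 does not disallow the class. Section 4.3 bars anyone who meets any one criterion, and Section 6.2.1 admits only people who meet none. Passing (8) does not undo failing (5), so on a strict reading the person is ineligible.

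**Step 3. Apply the rules to a subject who starts the drug on treatment.** Exclusion (5) no longer operates. Table 5-1 and footnote a apply, and co-administration is allowed under their conditions. The protocol does not say why the two cases differ.

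**Step 4. Effect on eligible/screened (illustration only).** Let e be the share of screened people eligible apart from this drug class, and q the share of those who are taking it when eligibility is decided. The protocol gives neither, so both are assumptions.

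- Ratio if Table 5-1 were followed: e
- Ratio under exclusion (5): e × (1 − q)
- Gap: e × q

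| e | q = 0 | q = 5% | q = 10% | q = 20% |
| --- | --- | --- | --- | --- |
| 30% | 30.0% | 28.5% | 27.0% | 24.0% |
| 50% | 50.0% | 47.5% | 45.0% | 40.0% |
| 70% | 70.0% | 66.5% | 63.0% | 56.0% |

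Entries are the ratio under exclusion (5). For q from 5% to 20% the gap runs from 0.30 × 0.05 = 1.5 points to 0.70 × 0.20 = 14 points. With q = 0 there is no gap. If e = 50% and every eligible person enrolls, 30 enrolled need 30/0.50 = 60 screened under the Table 5-1 reading. Under exclusion (5) they need 30/0.475, 30/0.45 and 30/0.40, or 64, 67 and 75 after rounding up. Only the direction is secure: exclusion (5) can lower the ratio but cannot raise it.

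**The case against.** The strongest reply is that the protocol already decides the case. The synopsis points to Sections 4.2 and 4.3 for detailed eligibility, any single exclusion suffices, and nothing in Section 5.2 declares a user eligible. Footnote a concerns taking the two drugs together, which can happen only once dosing has begun. The 21-day window in Section 5.2 is attached to prohibited drugs, so it does not clearly reach a class in the caution column. Being stricter at entry than on treatment is a coherent design.

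Most of this stands. A reader might infer that a current user cannot be classified, or is equally eligible and ineligible depending on the section. The documents do not support that, because the decision rule in Section 4.3 settles it. What the reply does not explain is why every other class in exclusion (5) is disallowed in Table 5-1 and this one is not. That pattern looks more like a drafting mismatch than a deliberate two-stage rule, and no sentence states such a rule.

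A second reply is that the effect on the endpoint is conjecture. That also stands. The illustrated 2.5 to 10 points at e = 50% lie within the sampling margin: with 60 screened, the 95% half-width at 50% is 1.96 × √(0.25/60) = 12.7 points. Someone who stops the drug before enrollment may not count as taking it, since exclusion (5) has no washout, and that would shrink q further. Nothing in the protocol shows that staff applied two rules.

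Third, Section 4.1 says that thirty subjects are already enrolled and one more is planned, so an edit governs one further entry. This limits its effect on conduct. It does not remove the need to report which rule was used.

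**Conclusion.** The mismatch is real and rests on the text alone: exclusion (5) bars a class that Table 5-1 does not disallow and footnote a lets subjects take with study drug. Read strictly, Section 4.3 governs entry and a current user is ineligible. The defect is that Section 5.2 treats the same class as usable, so staff relying on it could reach the opposite answer, and entry and on-treatment use follow different rules without explanation.

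The effect on eligible/screened is of unknown size and may be zero. The 1.5 to 14 point range holds only under the assumed values of e and q, so a reader should not infer that the primary measure is off by any particular amount. The point is worth correcting because it touches entry, drug exposure and a primary measure. It does not undermine the pilot. Which rule is clinically right is not judged here.

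**What to change.** Reconcile exclusion (5) with Table 5-1 and footnote a. The sponsor's clinical lead should choose the rule and state whether use at entry and use started on treatment are meant to be handled differently. This should be settled before the additional subject is enrolled.

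In the screening summary:

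- State which rule was actually applied.
- Report the number excluded under (5) for proton-pump-inhibitor use. Section 10.1.5 already requires the reason a consented person was not enrolled to be documented.
- Report the number enrolled while taking one.
- Show people without a medication record as unknown. In Appendix 1, concomitant medications are a screening item but lack the asterisk that marks what must be done at the first screening visit, so people who failed there may have no record.

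The cost is a short protocol edit, which needs IRB approval like any modification, and one or two extra rows in the screening summary. No new data collection is needed.

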## Pretreatment Assessments

### Screening Visits

Subjects will be screened within 30 days of enrollment to determine eligibility for participation in the study. The screening window can be extended to 42 days in exceptional circumstances. Subjects meeting all of the inclusion criteria and none of the exclusion criteria will return to the clinic within 30 days after screening for enrollment into the study.

After consent is obtained and eligibility is determined, screening assessments (split between two visits) will include medical history and physical examination (including weight and height), review of systems, vital signs, concomitant medications, CBC with diff/CMP, PT/INR, HBsAg, HCV RNA, HCV genotype and sub-type (or lab documentation during period of diagnosis of chronic HCV), urine drug screen, HIV Ag/Ab test, and stored sample for potential HCV sequence analysis.

Subjects will be compensated $15 for screen 1 and $15 for screen 2.

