### Enrollment Visit

Enrollment tests and procedures will be completed prior to enrollment and dosing/dispensing of study drug.

Enrollment visit will include a urine drug screen, urine β‑hCG (females of childbearing potential only), vital signs, randomization to study arm, motivational interviewing–based counseling pertaining to risk reduction and medication adherence, administration of the Audio Computer Assisted Self Interview (ACASI), and medication dispensation (unobserved dosing) or first directly observed dosing (mDOT).

Subjects will be randomized 2:1 to mDOT (n=20) or unobserved dosing (n=10) using permuted blocks of randomly selected sizes 2 and 4 generated using a STATA computer program. Staff members who have no contact with study participants will enclose and seal treatment allocation cards in sequentially numbered opaque envelopes to correspond with the randomization sequence. As a participant is enrolled, the envelope that corresponds with their sequence will be opened to reveal their randomized treatment condition.

mDOT subjects will receive a 10-trip Muni card to cover weekly round-trip transportation to study site and the unobserved dosing arm will receive a weekly two-trip Muni card to cover round-trip transportation to study site. These cards will be dispensed at weekly visits only so as to avoid directly compensating participants for attending daily visits.

Subjects will be compensated $20 for the enrollment visit.

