**APPENDICES**

Appendix 1. Study Procedures Table

Appendix 2. Estimating Severity Grade for Parameters Not Identified in the Grading Table

Appendix 1. Study Procedures Table

Screening, Weekly Visits (mDOT and unobserved dosing arms), and Post-Treatment Visits

| Clinical Assessments | | Screening visits | Enrollment | Visit identified by study week | | | | | | | | | | Post-treatment visits | | | |
| --- | --- | --- | --- | --- | --- | --- | --- | --- | --- | --- | --- | --- | --- | --- | --- | --- | --- |
|  |  | Day ‑30^a^to Day 0 |  | 1 | 2 | 3 | | 4 | 5 | 6 | 7 | 8 | 1 | | 12 | 36 | ET |
| Informed Consent | | X* |  |  |  |  |  | |  |  |  |  |  | |  |  |  |
| Determine Eligibility | | X* |  |  |  |  |  | |  |  |  |  |  | |  |  |  |
| Medical History ^b^ | | X |  |  |  |  |  | |  |  |  |  |  | |  |  |  |
| Physical Examination | | X |  |  |  |  | X | |  |  |  | X |  | |  |  | X |
| Review of systems | | X |  |  |  |  |  | |  |  |  |  |  | |  |  |  |
| Height and weight | | X |  |  |  |  |  | |  |  |  |  |  | |  |  |  |
| Vital Signs ^c^ | | X | X |  |  |  | X | |  |  |  | X |  | |  |  | X |
| Concomitant Medications | | X |  | X | X | X | X | | X | X | X |  |  | |  |  | X |
| Adverse Events | |  |  | X | X | X | X | | X | X | X | X | X | | X | X | X |
| PT/INR | | X |  |  |  |  |  | |  |  |  |  |  | |  |  |  |
| CBC with diff/CMP | | X |  |  | X |  |  | |  |  |  | X |  | |  |  | X |
| HCV RNA (Plasma) | | X |  |  | X |  |  | |  |  |  | X |  | | X | X | X |
| Urine β‑hCG ^d^ | |  | X |  |  |  |  | |  |  |  |  |  | |  |  |  |
| Urine Drug Screen | | X* | X | X | X | X | X | | X | X | X | X | X | | X | X | X |
| HCV Genotyping^e^ | | X |  |  |  |  |  | |  |  |  |  |  | |  |  |  |
| HIV Ag/Ab | | X |  |  |  |  |  | |  |  |  | X |  | |  |  | X |
| HBsAg | | X |  |  |  |  |  | |  |  |  |  |  | |  |  |  |
| Stored dried blood spots | |  |  | X | X | X | X | | X | X | X | X |  | | X | X | X |
| Stored samples for SOF and LDV metabolite level | |  |  |  | X |  | X | |  |  |  | X |  | |  |  | X |
| Stored samples for HCV sequence analysis | | X |  |  |  |  |  | |  |  |  | X |  | | X | X | X |
| Randomization to study arm | |  | X |  |  |  |  | |  |  |  |  |  | |  |  |  |
| Motivational-Interviewing based medical adherence counseling | |  | X |  |  |  | X^f^ | |  |  |  |  |  | |  |  |  |
| Motivational-Interviewing based risk reduction counseling | |  | X |  |  |  |  | |  |  |  |  | X | | X |  |  |

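### Exclusion (8) sets one 21-day window for all prohibited drugs, while Section 5.2 bars amiodarone from 60 days before enrollment

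*Protocol*

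**What the plan says.** **Eligibility list.** Protocol Section 4.3, exclusion (8), excludes "Use of any prohibited concomitant medications as described in Section 5.2 within 21 days of the enrollment visit". It gives one figure for every drug that it covers.

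**Medication rules.** Section 5.2 gives two windows. Prohibited drugs in general are barred from 21 days before enrollment to the end of treatment. Amiodarone has its own, longer period of 60 days before enrollment, set in bold in the body text. Footnote c of Table 5-1 repeats it: "The use of amiodarone is prohibited from 60 days prior to Baseline/Day 1 through the end of treatment". The same footnote gives the reason: "May result in symptomatic bradycardia. Mechanism is not currently known". The table places amiodarone in the disallowed column, not the caution column, so it is among the drugs that exclusion (8) reaches.

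**How the list is used.** Section 6.2.1 ties entry to the Section 4 criteria: "Subjects meeting all of the inclusion criteria and none of the exclusion criteria will return to the clinic within 30 days after screening".

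**What is recorded.** Section 5.2 states: "Concomitant medications taken within 30 days prior to screening will be recorded in the source documents". Section 6.10.2 (Medical History) adds a medication history at screening, with no stated look-back.

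**Who is still to come.** Section 4.1 reports thirty subjects enrolled and plans one more under the same rules.

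**The concern.** The criterion that decides entry is looser than the rule it cites. For most prohibited drugs the two sections agree on 21 days. For amiodarone they do not, and this is the one drug for which the authors wrote a separate window and attached a cardiac safety reason to it. A reader who takes the list of drugs from Section 5.2 and the window from exclusion (8) would regard amiodarone stopped four weeks ago as acceptable. Section 5.2 says that use in that period is prohibited.

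The stake is the safety of a participant and the consistency of the eligibility record. Nothing in the statistical analysis depends on it.

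**Working it through.** No sample-size, power or error-rate figure is involved. The check sets the criteria side by side and uses simple day counts.

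**Step 1. Which listed criterion excludes a person by time since the last amiodarone dose?**

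| Last dose before enrollment | Exclusion (5) | Exclusion (8) | Section 5.2 |
| --- | --- | --- | --- |
| Still taking | Not named in its list | Excluded | Prohibited |
| Up to 21 days | Not named in its list | Excluded | Prohibited |
| 22 to 60 days | Not named in its list | Not excluded | Prohibited |
| More than 60 days | Not named in its list | Not excluded | Not prohibited |

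Exclusion (5) concerns drugs being taken now. Its list covers proton-pump inhibitors, certain anticonvulsants, rifamycins, rosuvastatin and certain herbs. The third row is the conflict. No other listed criterion names amiodarone or a 60-day window.

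**Step 2. Width of the gap.**

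Gap = Section 5.2 window − exclusion (8) window = 60 − 21 = 39 days (days 22 to 60 inclusive).

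**Step 3. Does the required medication record close the gap?** Let S be the number of days from the screening visit at which medications are recorded to enrollment. The record must start 30 days before screening, so it reaches back 30 + S days before enrollment. To cover 60 days:

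30 + S ≥ 60, so S ≥ 30.

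Section 6.2.1 sets the ordinary limit at 30 days and adds: "The screening window can be extended to 42 days in exceptional circumstances".

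| S (days) | Reach, 30 + S (days) | Short of 60 by (days) |
| --- | --- | --- |
| 0 | 30 | 30 |
| 10 | 40 | 20 |
| 20 | 50 | 10 |
| 30 (ordinary limit) | 60 | 0 |
| 42 (exceptional limit) | 72 | 0 |

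The protocol fixes only the upper limits of S; the other rows are illustrations. The record alone guarantees 60 days only at the end of the ordinary window or in the exceptional extension. The medication history in Section 6.10.2 may supply the rest, but no period is set for it. Even where earlier use is on record, comparing it with exclusion (8) as written gives the wrong answer for days 22 to 60.

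**Step 4. Effect of the correction.** With a 60-day exception for amiodarone in exclusion (8), the gap becomes 60 − 60 = 0 days.

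**The case against.** The best defence is that the correct rule is present and hard to miss. Exclusion (8) names no drug, so staff cannot apply it without opening Section 5.2, where the 60-day rule appears twice. Section 10.1.9 makes the investigator responsible for following the protocol as a whole. Exclusion (10) lets the investigator exclude anyone with a condition judged to preclude participation. The medication history has no time limit, and Section 6 refers to a procedures manual that is not at hand and may ask the question directly.

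Much of this stands. It is why the claim is that staff *could* accept such a person, not that they would. It does not reconcile the text. The reference to Section 5.2 identifies the drugs, but exclusion (8) then states its own window; if it imported the windows from Section 5.2, the 21 days would have no function. Exclusion (10) names neither a drug nor a period.

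A reader might infer more than the documents support in four ways:

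- *That the protocol has no 60-day rule.* It has one, in Section 5.2. The fault is that the eligibility list does not carry it.
- *That Section 5.2 says outright that such a person must not be dosed.* It says that use of the drug in that period is prohibited. Withholding treatment is a reasonable inference, not its wording.
- *That 39 of 60 days, or 65%, measures risk.* It is a share of calendar days. It says nothing about how many people take amiodarone or how bradycardia risk falls after stopping it.
- *That the enrollment visit schedule is part of this contradiction.* Section 6.2.2 places "medication dispensation (unobserved dosing) or first directly observed dosing (mDOT" at that visit and lists no medication review there, and Appendix 1 leaves the concomitant-medication row blank for it. That affects every prohibited drug and is a separate matter from the 21-day and 60-day conflict.

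**Conclusion.** The contradiction holds. Read literally, exclusion (8) lets through a person 22 to 60 days after the last amiodarone dose, a 39-day span in which Section 5.2 prohibits the drug on safety grounds. No other listed criterion specifically closes the gap. The safeguards elsewhere in the protocol reduce the chance of an error but do not remove the conflict.

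Its size is small. One planned subject remains to be enrolled. The protocol gives no rate of amiodarone use, so no number of affected subjects is claimed, and nothing in the documents suggests that any of the thirty already enrolled had used it. No estimate, test or interval changes.

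The conclusion rests on two readings: that the 21 days in exclusion (8) apply to every drug it covers, as the wording states, and that the reach of the medication record is counted from the screening visit at which it is taken. This is a minor safety-consistency correction, worth making because the rule is wrong as written and still has one use ahead of it.

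**What to change.** Amend exclusion (8) so that its window reads: *within 21 days (60 days for amiodarone) of the enrollment visit*. Ask the remaining subject about amiodarone use in the previous 60 days, before the first dose is observed or dispensed, and document the answer.

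The cost is one parenthetical in Section 4.3 and one question. Under Section 10.2.1 the change goes to the IRB as a protocol modification, with approval before use and notice to the company named there. No visit, sample or analysis is added.
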